## Abstract

**Background:**

Hypertension is a risk factor for cardiovascular disease, and the prevalence of hypertension tends to increase with age. Current treatments for hypertension have side effects and poor adherence. Qigong has been studied as an alternative therapy for hypertension; however, the types of qigong used in those studies were diverse, and there have not been many well-designed randomized controlled trials.

Our objectives are the following: 1) To evaluate the effects of qigong on blood pressure, health status and hormone levels for pre- or mild hypertension. 2) To test the methodological appropriateness of this clinical trial and calculate a sample size for future randomized trials.

**Methods:**

Forty subjects with pre- or mild hypertension will be randomized to either the qigong exercise group or the non-treated group. Participants in the qigong group will conduct qigong exercises 5 times per week for 8 weeks, and participants in the non-treated group will maintain their current lifestyle, including diet and exercise. The use of antihypertensive medication is not permitted. The primary endpoint is a change in patient blood pressure. Secondary endpoints are patient health status (as measured by the SF-36 and the MYMOP2 questionnaires) and changes in hormone levels, including norepinephrine, epinephrine, and cortisol.

**Discussion:**

This study will be the first randomized trial to investigate the effectiveness of qigong exercises for the treatment of pre- and mild hypertension. The results of this study will help to establish the optimal approach for the care of adults with pre- or mild hypertension.

**Trial registration:**

Clinical Research Information Service KCT0000140

## Background

Hypertension is a risk factor for future cardiovascular events, including heart attack, heart failure, and stroke, which are the most frequent causes of death in developed countries [1,2]. Hypertension affects approximately one billion individuals worldwide, and the prevalence of hypertension tends to increase with age [3]. In Korea, hypertension affects more than 30% of people over the age of 30 and up to 65% of people over 65 [4].

Current interventions for hypertension include sodium restriction, pharmacological management, and lifestyle modifications, such as stress management and exercise. However, in clinical practice, hypertension can be difficult to control, due to poor adherence to prescribed interventions [5]. Lifestyle interventions are difficult to achieve and maintain, and antihypertensive medications present risks of side effects.

Qigong is a common healing technique in Oriental medicine and has been used clinically for preventing and curing disease, as well as for improving and maintaining overall health [6]. It has been claimed that qigong can foster health and healing by promoting the smooth flow of qi throughout the body so that the body can heal itself [7]. Qigong includes two concepts: qi, the vital energy of the body, and gong, the training or cultivation of qi. Medical qigong is divided into internal and external components. Internal qigong consists of exercises, including breathing, meditation, focus of intention and rhythmical movements, while external qigong is performed by a trained practitioner in order to deliver qi energy to the patient [8]. It is generally accepted that internal qigong is the more beneficial aspect for the promotion of good health [9].

Qigong has been found to have effects on various conditions, such as cancer [10-12], pain [13] and diabetes [14]. Qigong has also been studied as an alternative therapy for controlling blood pressure. Previous such research has concluded that patients with essential hypertension practicing qigong for less than 1 year had improved blood pressure (BP) control compared with non-treated controls [7].

However, well-designed rigorous randomized controlled trials (RCTs) related to the effects of qigong on BP control are still scarce [15]. Although most qigong trials have targeted essential hypertension, the stages of hypertension exhibited by study subjects were diverse, and some studies did not describe each patient's exact blood pressure. In addition, there has been no trial assessing the effects of qigong on pre-hypertension. To assess the effects of qigong for pre- and mild hypertension through a high-quality RCT, a pilot study to evaluate qigong should be conducted.

The aims of this pilot study are the following: (1) to evaluate the effects of internal qigong on blood pressure, health status and hormone levels in patients with pre- or mild hypertension and (2) to test the methods and calculate a sample size for future randomized trials to investigate further the clinical value of qigong in controlling hypertension.

## Methods/Design

### Study design

The study is a 2-parallel group, randomized controlled trial to compare qigong with no treatment for pre- and mild hypertension on the following outcomes: blood pressure, Health Related Quality of Life (HRQOL), clinical symptoms and hormone levels. The study design is depicted in Figure 1.

**Figure 1 F1:**
[figure not shown]
**Flowchart of the study design**.

### Ethics

The protocol has been approved by the institutional review boards of Dongeui University, where the study will take place. This study has been registered with the 'Clinical Research Information Service', Republic of Korea, which is a registry in the WHO Registry Network [16].

This study will be monitored by an independent data and safety monitoring board. Advertisements for voluntary subjects will be printed in local newspapers and posted on notice boards in the local community. All of the participants will provide written informed consent.

### Participants

#### Inclusion criteria

The inclusion criteria are as follows: (1) patient age between 19 and 65 years, (2) systolic blood pressure between 120 and 159 mm Hg and/or diastolic blood pressure (DBP) between 80 and 99 mm Hg as measured in a sitting position, and (3) the absence of objective signs of hypertension end-stage disease.

#### Exclusion criteria

The exclusion criteria are as follows: (1) serious symptomatic cardiac disease, including previous myocardial infarction, angina or heart failure; (2) previous transient ischemic attacks or stroke; (3) secondary hypertension; (4) taking medications that could affect hypertension, such as stimulants, central nervous system depressants; (5) necessity of antihypertensive medications; (6) concomitant illness that precludes participation, including diabetes, cancer, infectious disease, renal failure; (7) pregnancy or the possibility of pregnancy; (8) moderate to high risk of cardiac complications during exercise; or (9) inability to comprehend and complete the study assessments or comply with the study instructions (Table 1).

**Table 1 T1:** Eligibility criteria

Inclusion criteria	Exclusion criteria
19-65 years of age	Serious symptomatic cardiac disease, including previous myocardial infarction, angina or heart failure

Pre- or Stage 1 hypertension -Systolic blood pressure between 120 and 159 mm Hg - Diastolic blood pressure between 80 and 99 mm Hg	Previous transient ischemic attacks or stroke

No objective signs of hypertension end-stage disease	Secondary hypertension

	Taking medications that could affect hypertension

	Necessity to continue antihypertensive medications

	Concomitant illness that precludes participation, including diabetes, cancer, infectious disease, renal failure

	Pregnancy or chance of pregnancy

	Moderate to high risk for cardiac complications during exercise

	Inability to comprehend and complete study assessments or comply with study instructions

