#### Collection of demographic and lifestyle information

Each patient's medical history, including current medication, surgical history, and the presence of other diseases, will be recorded at baseline. Lifestyle factors, including diet, exercise, smoking, and drinking alcohol, will also be documented. To investigate other risk factors for hypertension, height, weight, waist and hip circumference, and other demographic information will also be measured. Body-fat percentage will be estimated by measuring bioelectrical impedance. A questionnaire for syndrome differentiation will be used based on general condition, sweating, pain, sleeping, breathing, skin and pulse.

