#### Non-treated group

The control group will receive no instruction in qigong exercise. They will be asked to maintain their routine lifestyle, including diet, exercise, work and other activities.

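### Regular qigong practitioners are not excluded; if any enrol, those assigned to qigong may have less left to gain, and the pilot's effect estimate would shrink

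*Protocol article*

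**What the plan says.** The Inclusion criteria section sets an age range, a blood-pressure range and "the absence of objective signs of hypertension end-stage disease". The Exclusion criteria section has nine items, and Table 1 repeats them. Only one item mentions exercise, "moderate to high risk of cardiac complications during exercise", and it is a safety rule. The last, "inability to comprehend and complete the study assessments or comply with the study instructions", concerns ability to take part. No item concerns current or past qigong practice.

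For controls, the Non-treated group section says: "The control group will receive no instruction in qigong exercise". It continues: "They will be asked to maintain their routine lifestyle, including diet, exercise, work and other activities". The abstract agrees: "participants in the non-treated group will maintain their current lifestyle, including diet and exercise".

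The section on demographic and lifestyle information says: "Lifestyle factors, including diet, exercise, smoking, and drinking alcohol, will also be documented". That record does not name qigong and has no stated role in eligibility. Age and sex are the only randomisation strata. Under Data analysis, baseline variables become covariates only when the arms differ significantly on them.

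The Study design section sets qigong against no treatment. The Background, Sample size and Discussion sections say that the pilot is to supply a sample size, and an effect size, for larger trials.

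**The concern.** The exposure under test is not screened for at entry. The Background says "Qigong is a common healing technique in Oriental medicine", and recruitment is by advertisement to local volunteers, so an existing practitioner with blood pressure in range could come forward and would be eligible.

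If assigned to qigong, that person may add little to what the baseline reading already reflects. The arm's mean change is then an average over people starting the exercise and people continuing something like it. The pilot's main product is a between-group effect for planning. A diluted value understates what qigong does in people who do not yet practise it, and makes the next trial larger than that population would need. With 20 per arm, each such person is 1/20 = 5% of an arm.

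**Working it through.** The plan's own figure, 20 per group, rests on citations. No effect size, standard deviation or power is given, so it cannot be reproduced, and this point does not need it.

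**Inputs from the protocol article**
- 20 per group, 40 in total (Sample size).
- Primary endpoint: change in blood pressure from baseline to 8 weeks (Outcome measures, Discussion), compared by ANCOVA (Data analysis).

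**Assumptions, because the document gives no value**
- p: share of participants already practising, equal in the two arms in expectation because of randomisation.
- r: fraction of the full effect that a practitioner still gains when assigned to the programme.
- Δ: full effect on change in someone not already practising; c: mean change in controls.
- The standard deviation is unaffected.

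**Step 1: mean change in each arm**
- Control: a person with a stable practice carries its effect in both the baseline and the week-8 reading, so the expected change is c, as for other controls.
- Qigong: (1 - p)(c + Δ) + p(c + rΔ).
- Difference: (1 - p)Δ + prΔ = Δ[1 - p(1 - r)].

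All of the shrinkage comes from practitioners in the qigong arm.

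**Step 2: effect on a later sample size**

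Required n varies as 1/effect², so it is multiplied by 1/[1 - p(1 - r)]².

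| p | people per arm of 20 | r | effect factor | n ratio |
|---|---|---|---|---|
| 0 | 0 | any | 1.00 | 1.00 |
| 10% | 2 | 0 | 0.90 | 1/0.81 = 1.23 |
| 20% | 4 | 0 | 0.80 | 1/0.64 = 1.56 |
| 10% | 2 | 0.5 | 0.95 | 1/0.9025 = 1.11 |
| 20% | 4 | 0.5 | 0.90 | 1/0.81 = 1.23 |

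For scale, at an assumed true standardised effect of 0.5, with 80% power and two-sided alpha 0.05 (normal approximation), n per arm is 63 undiluted, 78 at p = 10% and 99 at p = 20%, both with r = 0.

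**Step 3: chance that any practitioner enrols**

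The prevalence among volunteers is not given. If it were 2%, the chance of at least one among 40 would be 1 - 0.98^40 = 55%. If it were 5%, it would be 1 - 0.95^40 = 87%.

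**Step 4: does another part of the plan correct this?**

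Stratifying by age and sex does not touch it. The covariate rule responds only to imbalance, whereas the factor in step 1 applies when practitioners are evenly split. The lifestyle record could support a description if it captured qigong, but it does not name it.

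**The case against.** A reader might infer that practitioners in the control arm, told to keep up their usual exercise, pull the control result towards the qigong result, so that exposure dilutes the contrast from both sides. The documents do not support that. The endpoint is change from baseline, and a practice that continues unchanged is already in the baseline reading. Such people are not qigong-naive, which fits poorly with a comparison against no treatment, but they do not shift the control mean change.

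The other objections bear on size:
- Practitioners may still gain. The programme is newly developed, with three instructor-led classes a week plus home practice, and the article says that earlier trials used diverse forms of qigong. Someone doing another form at another dose is not already receiving it. This stands, and r = 0 is an upper bound.
- Prevalence is unknown. Calling qigong common in Oriental medicine does not say how many local volunteers practise it. This stands, so the point must remain conditional.
- A later trial with the same criteria and a similar mix would face the same dilution, so the pilot's effect would be the right planning value. This stands in part: the n ratios measure a planning error only if the later trial enrols non-practitioners. Otherwise they are the price of keeping the criteria.
- Dilution is small beside sampling error. With 20 per arm, the 95% interval for a standardised difference is about ±1.96 × √(2/20) = ±0.62, while 10% of an assumed effect of 0.5 is 0.05. This is true, but more precision would not remove the dilution.
- Admitting people whatever their exercise history gives the effect of adding the programme to usual habits, a legitimate question. The article does not say that this is the intended one.

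**Conclusion.** The point holds in conditional form. The eligibility list is presented as complete, appears twice, and does not screen for existing practice of the intervention under test. If a share p already practises and keeps a fraction r of the possible gain, the expected difference is 1 - p(1 - r) times the full one. At p of 10% to 20% that is a loss of 10% to 20% with r = 0, or 5% to 10% with r = 0.5. It is nil if no practitioner enrols. These figures rest on assumed p and r, a stable practice in controls and an unchanged standard deviation.

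This is not confounding, because randomisation balances prior practice in expectation. Nor does the document contradict itself here. It is an inexpensive improvement to the estimate that the pilot exists to supply.

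**What to change.** Add one exclusion criterion, in the text and in Table 1, for current or recent regular qigong practice. The sponsor should define what counts as regular and state the look-back period. The clinical research coordinator can ask about it at the existing telephone screen and enter the answer in the screening log.

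Optionally, state that controls should not take up qigong before the follow-up visit four weeks after the 8-week period. This is secondary, because the request to keep to their routine largely implies it, and it addresses new uptake rather than existing practice.

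The cost is one line and one question, a slightly smaller pool for 40 places, and results that apply only to people not already practising qigong.

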#### Participant recruitment

We will recruit 40 participants; all participants will provide written consent before participation in the study. The clinical research coordinator (CRC) will initially screen by telephone each potential participant against the inclusion and exclusion criteria. Willing potential participants will be given an appointment at the center for the qigong trial. A screening log will be maintained to record the inclusion/exclusion criteria for all those participants. The CRC will briefly explain the purpose of the study and ask if they have an interest in participating. The CRC will also record basic demographic and medical information.

#### Sample size

There are no previous clinical trials to evaluate the effect of qigong on pre- or mild hypertension. Therefore, this study is designed as a pilot study to calculate the appropriate sample size for future randomized clinical trials. Each group will include 20 participants, which is the minimum sample size for evaluating the effect of qigong [17,18].

#### Randomization and allocation concealment

The subjects admitted to the trial will be randomized to either the qigong group or the non-treated group. Participants will be randomized before the first treatment by an online centralized randomization service. Randomization will be stratified by age and sex.

Allocation concealment will be ensured, as the service will not release the randomization code until the patients are recruited into the trial after all baseline measurements are completed.

#### Collection of demographic and lifestyle information

Each patient's medical history, including current medication, surgical history, and the presence of other diseases, will be recorded at baseline. Lifestyle factors, including diet, exercise, smoking, and drinking alcohol, will also be documented. To investigate other risk factors for hypertension, height, weight, waist and hip circumference, and other demographic information will also be measured. Body-fat percentage will be estimated by measuring bioelectrical impedance. A questionnaire for syndrome differentiation will be used based on general condition, sweating, pain, sleeping, breathing, skin and pulse.

#### Blinding

Outcome assessors will be blind to group allocation and will not be involved in providing intervention. However, it will be difficult to blind the participants because the control group will not receive any intervention.

### Intervention

#### Qigong exercise

Although there have been several qigong trials for hypertension, the type of qigong used in those trials was diverse, and there has been no standardized qigong exercises for the treatment of hypertension. We have developed a qigong protocol for the treatment of hypertension based on discussions with three qigong professionals.

Qigong will be taught by an instructor with expertise in qigong. The participants will visit the clinic and take 3 qigong classes per week for 8 weeks. Each qigong class lasts 30 minutes, including a warm-up (5 min) and a cool-down (5 min) portion. In addition, the subjects will be asked to practice qigong at home for 30 min more than 2 times a week for the duration of the study. The purpose of qigong exercise is to improve kidney and liver function, to improve blood circulation and to lower blood pressure through calming (Table 2).

**Table 2 T2:** Composition of Qigong

Stage	Stage	Motions
Warm-up	1	Meditate for 1 minute, swing your arms and shoulders and flex your waist, knees and ankles.
1^st^	1	Lift both hands overhead, locking your fingers together while bending and extending your knees.
	2	Lean your body to the right while breathing in, and stand straight, while breathing out. Repeat 4 times to the left and right, alternating.
2^nd^	1	Advance your left foot, and lower your right hand from the left of your head to your right leg drawing an oblique line quickly. Repeat this 8 times to the left and right, alternating.
3^rd^	1	Advance your right foot, lift your right arm and support your right elbow with the back of your left hand.
	2	Lower your body quickly while bending your knees and clenching your right fist. Repeat this 8 times to the left and right, alternating.
4^th^	1	Advance your left foot and put your left hand on your left knee. Put your right hand on your left hand and push down as much as possible. Lift up right hand to the right. Repeat this 8 times to the left and right, alternating.
5^th^	1	Put your feet apart and relax your wrists and lift your hands slowly forward.
	2	Lower your hands while bending your knees. Repeat this 10 times.
6^th^	1	Support your back with your hands and lean back.
	2	Bend your waist forward and sweep the back of your legs with your hands.
	3	With straight waist, lift your hands overhead while breathing in and lower them, while breathing out. Repeat this 8 times.
7^th^	1	Put your feet apart and twist your body backward to the left.
	2	Reverse your palms and gather them on your forehead.
	3	Look straight ahead slowly again. Repeat this 8 times to the left and right, alternating.
8^th^	1	Lift your arms to the right.
	2	Lower your body while crossing your left leg backward, and stand straight. Repeat this 10 times to the left and right, alternating
9^th^	1	Bend your knees and lift your arms in parallel and make a circle.
	2	Extend your knees and spread your arms. Twist your upper body backward to the right.
	3	Stand straight while breathing out. Repeat this 8 times to the left and right, alternating.
10^th^	1	With your left foot advanced, lift your right arm up. Tap the area of your liver with your left hand 14 times. Repeat this movement 2 times.
Cool-down	1	Bend your knees and lift up your arms shoulder high. Put your feet apart while breathing in, and gather your feet while breathing out. Repeat this movement 10 times to the left and right, alternating.
	2	Concentrate your mind on an acupoint KI1 on the bottom of your foot for 1 minute.

The compliance of the subjects will be assessed in terms of the number of qigong classes attended and the number of home repetitions per week. No antihypertensive medications or medications that affect blood pressure will be permitted during the study.

#### Non-treated group

The control group will receive no instruction in qigong exercise. They will be asked to maintain their routine lifestyle, including diet, exercise, work and other activities.

### Outcome measures

#### Primary

The primary outcome will be changes in patient blood pressure before and after qigong exercises. Blood pressure will be taken at every visit. The subjects will be fitted with a BP cuff on the right arm and allowed to sit quietly for 5 minutes. A trained research nurse will measure the blood pressure carefully with the subject in the seated position 3 times after resting for at least 10 min in a temperature-controlled room. Three measurements will be carried out at 5-min intervals. The mean of these 3 measurements will be used in the data analysis.

Subjects will be instructed to wear loose and comfortable clothing. The investigators will refrain from wearing laboratory coats during all sessions, as the use of such apparel has been associated with increased BP in some patients (white-coat hypertension).

